### Inclusion/exclusion criteria

2.2.

The study participants in each cohort will meet all inclusion criteria to be eligible for this trial. For cohort 1, the patients will:

(1) have a diagnosis of autism as outlined by a child psychiatrist according to the Diagnostic and Statistical Manual of Mental Disorders (5th edition) and positive results on both the Autism Diagnostic Observation Schedule and Autism Diagnostic Interview-Revised assessments;(2) age 3–9 years, regardless of gender;(3) not have immunodeficiency disorders;(4) provide signed ICF by participants’ legal guardians who fully understand the study;(5) have an ABC score ≥ 62 at the time of screening;(6) meet two of the following scale scores at the time of screening: Childhood Autism Rating Scale (CARS) score ≥ 38; Social Responsiveness Scale (SRS) score ≥ 75.

For cohort 2, the patients will:

(1) age 3–9 years;(2) have a male to female ratio as close to cohort 1 as possible;(3) provide signed ICF by participants’ legal guardians who fully understand the study;(4) have normal physical examination, vital signs and important laboratory test results.

Subjects meeting any of the following exclusion criteria will not be allowed to participate.

(1) Use of probiotics, antibiotics, antifungal, prebiotic and other drugs affecting the intestinal microflora in a planned way within the last 3 months or in the following 6 months.(2) Diagnosis of intestinal obstruction (including partial obstruction), or severe ulcerative damage to the bowel;(3) Diagnosis of an immunodeficiency disorder or autoimmune disease, including but not limited to rheumatoid arthritis, systemic lupus erythematosus, ankylosing spondylitis, desiccation syndrome, Hashimoto’s thyroiditis, toxic diffuse goiter, autoimmune hemolytic anemia, idiopathic thrombocytopenic purpura, Crohn’s disease, psoriasis, glomerulonephritis, nephrotic syndrome;(4) A previous history of severe food or drug allergy;(5) A history of severe fever and/or severe infection within 7 days prior to enrolment;(6) Renal insufficiency and hepatic dysfunction, for instance, alanine aminotransferase level > 1.5 times the normal upper limits, aspartate aminotransferase level > 1.5 times the normal upper limits, or serum creatinine level > 1.5 times the normal upper limits;(7) Be in an immunosuppressed state (i.e., presence of a neoplastic disease or organ transplantation) underwent or undergoing chemotherapy;(8) Diagnosed with inflammatory bowel disease, celiac disease, irritable bowel syndrome or eosinophilia, oesophagitis, eosinophilic gastroenteritis or similar conditions;(9) Diagnosis of blindness, deafness, cerebral palsy, etc.;(10) Participation in another clinical study or an interventional clinical study with non-conventional rehabilitation within 4 weeks prior to enrolment;(11) A previous history of HIV, hepatitis B virus, hepatitis C virus or syphilis infection, or a parent with HIV infection;(12) A treatment of intra-abdominal surgery (excluding appendectomy or cholecystectomy) within the past 60 days prior to screening and/or planned invasive surgery/hospitalization during the study period;(13) Presence of certain prominent symptoms, including but not limited to stereotyped repetition, aggression, self-injury, vandalism, severe emotional behavioral problems and extreme hyperactivity, and requiring pharmacological treatment as per the principal investigator assessment;(14) Poor compliance (i.e., therapeutic drinks taken at less than 80%), using the following formulas to estimate:

Dose = total dose - remaining dose;Adherence rate (a quantitative indicator of adherence) = (dose taken/total amount) x 100%.

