### Study design

2.1.

This is a single-center, double-blind, double-modeled, randomized, interventional clinical study aiming at exploring the efficacy and safety of FMT formulation on an interventional treatment of children with ASD. The degree of improvement in their symptoms will be assessed using several scales. Additionally, changes in the composition and structure of their intestinal flora and metabolites of the flora in their blood, urine and feces before and after treatment will also be assessed by macro-genomic sequencing and metabolomics. The study will also evaluate the differences in the gut flora of children with ASD and healthy children and the acceptability of FMT pediatric preparations by children with ASD and their legal guardians.

The primary endpoint of the study is the change from baseline in Childhood Autism Rating Scale (CARS) scores in children with ASD after 12 and 24 weeks of treatment. The secondary endpoints are the variations in assessment scales, and gut flora and included five main points:

(1) Variations in scores from baseline in the Social Responsiveness Scale (SRS), Autism Behavior Checklist (ABC), Psychoeducational Profile Third Edition (PEP3), Gastrointestinal Symptom Rating Scale (GSRS), and Children’s Sleep Habits Questionnaire (CSHQ) after 12 and 24 weeks of treatment;(2) Variations in gut flora characteristics (including alpha-diversity, flora composition, beta-diversity, colonizing bacteria, differential bacteria, and metabolic pathway function) in children with ASD after treatment compared to baseline and donors;(3) Differences in intestinal flora characteristics (including alpha-diversity, flora composition, beta-diversity, differential bacteria, and metabolic pathway function) between children with ASD (baseline) and healthy children;(4) The incidence of adverse events during the treatment of children with ASD;(5) Variations in the FMT acceptance scale scores for participants with ASD and their legal guardians.

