#### Experimental flow

2.5.2.

##### Cohort 1

2.5.2.1.

The study flow for Cohort 1 will be divided into seven phases: screening period, bowel preparation, first treatment dose, intensive treatment, maintenance treatment, follow-up, and exit (Figure 2). The patients will undergo stool and urine sample collection, relevant examinations, and scale assessments (Table 1). During the screening period (D-21 ~ D-7), the eligible ASD patients will be assessed based on the implemented scales and complete all required examinations, and the baseline data will be recorded. In the bowel preparation phase (D-6 ~ D-1), patients in both the trial and control groups will undergo bowel preparation with oral rifaximin suspension or rifaximin mimetic for five days at 0.1 g each time, four times daily, followed by one day of polyethylene glycol bowel cleansing. The first treatment dose (D1 ~ D7) will involve administering a total of approximately 700 mL of the therapeutic drink (containing 66 mL of bacterial liquid or placebo) orally over 3 to 5 consecutive days of the week, depending on the subject’s acceptance of the therapeutic drink and the volume available for each dose. Intensive treatment (D8 ~ D28) will involve an intensive dose of approximately 60 mL of the treatment drink (containing 6 mL of bacterial fluid or placebo) once a week for 3 weeks. During the maintenance treatment phase (D29 ~ D84), once weekly doses of approximately 10 mL of the treatment drink (containing 0.6 mL of bacterial liquid or placebo) will be administered for 8 weeks. During the follow-up period (D85 ~ D169), the subjects will receive the same rehabilitation as during the treatment period. They will be discharged at week 25 after completion of the end-visit examination (D170). Throughout the treatment period, they will be asked to adhere to the “Dietary Manual for People with Autism Receiving FMT Therapy” as closely as possible, with a legal guardian completing a weekly dietary record form.

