## Discussion

5.

ASD is a complex and heterogeneous disease with multiple phenotypes. Its underlying cause is unknown, and no curative drugs or treatments are currently available. However, increasing evidence from animal studies and clinical research supported a link between the microbe-gut-brain axis and ASD (Cryan et al., 2019; Martinez-Gonzalez and Andreo-Martinez, 2020). Gastrointestinal symptoms are a common complication in children with ASD, with affected children four times more likely to experience symptoms such as diarrhea, constipation, and abdominal pain than non-ASD children (Patusco and Ziegler, 2018). Some of these symptoms, such as reflux and vomiting, can disrupt the daily activities of children with ASD and are often accompanied by other symptoms, such as an imbalanced intestinal flora, increased intestinal permeability, inflammation, and food allergies (Buie et al., 2010).

Furthermore, there were evidences suggesting that FMT may be effective in improving both ASD behavior and gastrointestinal symptoms by improving intestinal microecology. Preclinical experiments have shown that FMT could improve autistic behavior, and fecal bacteria from wild mice have been found to improve autistic behavior, metabolic levels, memory, and social skills in ASD mice (Li et al., 2020). Kang et al. used FMT in combination with antibiotics, omeprazole and Movi Prep therapeutic drinks, which increased the abundance of Bifidobacterium, Prevotella, and Desulfovibrio, leading to improvements in ASD and gastrointestinal symptoms that lasted for at least 8 weeks (Kang et al., 2019) which also led to changes in serum and intestinal metabolites (Kang et al., 2020). Li et al. found that FMT improved gastrointestinal symptoms and ASD symptoms, promoted a shift in the intestinal flora of children with ASD to that of typical neurological children, and significantly altered serum levels of neurotransmitters (Li et al., 2021). Additionally, Zhao et al. found that FMT was statistically different in improving gastrointestinal symptoms and ASD symptoms, improved gut microbiology, and caused only mild, transient adverse events in 29.2% of patients (Zhao et al., 2019). These studies demonstrate that FMT is a safe and effective treatment that contains at least 1,000–1,150 functional bacteria (Zhang et al., 2012), making it an ideal treatment option for improving gut microecology and the effectiveness of treatment for ASD.

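### Exclusion (1) applies the planned-use qualifier to the past 3 months as well as the next 6, so an unplanned recent antibiotic, antifungal, probiotic or prebiotic course does not exclude a child in either cohort

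*Protocol article*

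**What the plan says.** Section 2.2 of the protocol article gives separate inclusion lists for Cohort 1 (ASD) and Cohort 2 (healthy children), followed by one exclusion list for all subjects. Exclusion (1) covers "Use of probiotics, antibiotics, antifungal, prebiotic and other drugs affecting the intestinal microflora in a planned way within the last 3 months", and its qualifier and windows run in full as "in a planned way within the last 3 months or in the following 6 months". It contains no exception for study procedures.

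Section 2.1 uses baseline flora twice. Secondary endpoint (2) is the change in flora after treatment compared with baseline and with donors. Secondary endpoint (3) is "Differences in intestinal flora characteristics" between children with ASD at baseline and healthy children.

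Section 2.5.2.1 places screening, with the baseline stool sample, at D-21 to D-7. Bowel preparation follows at D-6 to D-1, when "patients in both the trial and control groups will undergo bowel preparation with oral rifaximin suspension or rifaximin mimetic for five days". The Discussion describes this step as antibiotic use.

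**The concern.** Planned use is a sensible limit for the future, because nobody can promise at screening that an acute infection will not need treatment. It is not a sensible limit for the past. A past course either happened or did not, and its effect on the flora does not depend on whether it was planned. In children aged 3-9 a recent antibiotic course is typically an unplanned response to an acute infection, so the qualifier removes the very exposure that the look-back exists to catch.

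Two secondary endpoints depend on this. In endpoint (3), a difference in recent exposure between the cohorts could be read as a marker of ASD, and randomisation does not protect this comparison. In endpoint (2), recovery from a recent course could look like a change after treatment when a group is compared with its own baseline.

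**Working it through.** **1. What the sentence admits.** The qualifier precedes the pair of windows (last 3 months, following 6 months) and is not repeated or limited to one of them. Read literally:

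| Use | Last 3 months | Following 6 months |
|---|---|---|
| Planned | excluded | excluded |
| Unplanned | not excluded | not excluded |

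The lower left cell is the gap.

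**2. Whether another criterion closes it.** Exclusion (5) covers only severe fever or severe infection in the 7 days before enrolment. A child who finished antibiotics for an ordinary infection two weeks before screening meets neither (1) nor (5). Exclusion (12) shows that the plan can separate past from future: intra-abdominal surgery in the past 60 days excludes outright, with two named exceptions, and only the study-period part is limited to planned events. Exclusion (1) does not follow that pattern.

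**3. Whether the analysis makes up for it.** Section 2.6 names Mann-Whitney U and Kruskal-Wallis tests for flora differences between groups and Spearman correlation. None of these adjusts for prior exposure. The limitations in the Discussion accept that factors affecting the flora are not fully considered. Eligibility is therefore the main safeguard.

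**4. Size, by assumption only.** The documents give neither an exposure rate nor the effect of a course on diversity. Assume that 10-30% of children had an unplanned course and that it lowers a diversity index by 1 SD.

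- Children affected: 0.10 × 42 = 4.2 to 0.30 × 42 = 12.6, about 4-13 with ASD; 0.10 × 30 = 3 to 0.30 × 30 = 9 healthy.
- Endpoint (3): false difference = (difference in exposure rates) × shift. With equal rates it is 0. With 30% in one cohort and 10% in the other it is (0.30 − 0.10) × 1 SD = 0.2 SD.
- Standard error of a 42-versus-30 mean difference: √(1/42 + 1/30) = 0.24 SD. The 0.2 SD is thus below one standard error.
- Endpoint (2), within a group: false change = exposure rate × shift = 0.1 to 0.3 SD if recovery is complete. This part is expected in both randomised arms.

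**5. Rifaximin and the baseline sample.** The baseline window closes at D-7 and bowel preparation opens at D-6. The trial's own rifaximin comes after the baseline stool sample and cannot alter it. What remains is a conflict of wording: exclusion (1) bars planned antibiotics in the next 6 months without exception, and section 2.5.2.1 schedules one.

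**The case against.** The wording can be read charitably as any use in the last 3 months and planned use in the next 6, and an investigator may well apply it so. That is probably the intention, but it is not what the sentence says. Exclusion (12) shows that the clearer form was available.

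Medical and treatment history is recorded at baseline in both cohorts, and Cohort 1 also has a combined medication record, so exposed children might be identified. Placebo randomisation means that recovery from earlier courses is expected in both arms of Cohort 1. Both arguments stand for the between-arm comparison, although 28 versus 14 children leaves room for chance imbalance. Neither protects the ASD-versus-healthy comparison: recording exposure does not exclude it, and the named tests do not use it.

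The same list screens both cohorts, so the threefold difference in exposure used above is chosen and not shown. That stands, and it is why the 0.2 SD is only an illustration.

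A reader might also infer that earlier FMT is admitted after too short a washout, because FMT is not named among the exclusions and exclusion (10) asks for only 4 weeks after another study. The documents do not support this. Three months is 89-92 days. The interval from the last dose (D78 to D84) to the end visit (D170) is 170 − 84 = 86 to 170 − 78 = 92 days, so the two are about equal. The only persistence figure, "leading to improvements in ASD and gastrointestinal symptoms that lasted for at least 8 weeks", is a lower bound of 56 days, which the 3-month window exceeds. Nothing indicates that candidates have had FMT, and a condensed article that does not name it is not in error. A ban on any previous FMT would be a preference, not a correction.

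**Conclusion.** The point holds as a defect of wording with a real but limited consequence. As written, exclusion (1) does not exclude unplanned use of antibiotics, antifungals, probiotics or prebiotics in the last 3 months, in either cohort. Secondary endpoint (3) is the most exposed because it is not randomised; the before/after part of endpoint (2) comes next.

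It would be too strong to say that baseline flora is unprotected: planned use in the last 3 months is still excluded. It would also be wrong to count the rifaximin bowel preparation as a cause, since it follows the baseline sample. The primary CARS comparison is randomised and not materially affected. No size can be derived from the documents; the figures above rest entirely on the assumed exposure rates and 1 SD shift. The correction is worth making because it is specific and cheap.

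**What to change.** Split exclusion (1) into two clauses. The look-back should cover any use of the listed agents in the last 3 months, planned or not, and apply to both cohorts. The look-forward should keep the planned-use qualifier for the following 6 months. No change to the length of either window is proposed.

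As a consistency edit, reconcile the look-forward ban on planned antibiotics in section 2.2 with the rifaximin bowel preparation in section 2.5.2.1, so that the two sections no longer contradict each other.

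The change is to eligibility wording only. Its cost is that some children will fail screening or have it delayed until the look-back is clear. If the assumed 10-30% were right, about that share of candidates would be affected, which a single centre should allow for in its recruitment timetable. If children have already been enrolled under the present wording, the baseline treatment history could be used to list recent unplanned use by cohort, as far as it captures such courses.

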The patients will be divided into two cohorts: Cohort 1 will include 42 children aged 3–9 years diagnosed with ASD, while Cohort 2 will include 30 healthy children aged 3–9 years. The sex ratio and age range of children enrolled in Cohort 1 and Cohort 2 will be kept roughly the same. In Cohort 1, subjects who meet the entry criteria will undergo a two-week screening visit after the legal guardian signs the informed consent. They will then be randomly allocated to either the trial or control group in a 2:1 ratio. Children in the trial group will undergo rehabilitation and FMT, while the control group will receive rehabilitation and placebo. All children will undergo a 12-week treatment period following the completion of bowel preparation and followed up for 12 weeks, during which they will receive only rehabilitation. A homogenous rehabilitation scheme will be performed on all the ASD children in Cohort 1. The study participants will be discharged at week 25 after the end visit. In Cohort 2, after the legal guardian signs the informed consent, they will undergo a physical examination, assessment of vital signs, and various laboratory examinations within two weeks to confirm their health status. Blood, urine, and fecal samples will be collected within one week, and the children will be discharged. Metabolomics analysis will be performed on blood and urine samples, while macro-genomic sequencing and metabolomics analysis will be conducted on fecal samples.

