### Randomization and blinding

2.4.

The Interactive Web Response System (IWRS) will be used to randomize subjects in Cohort 1. Prior to enrollment, a random coding table will be generated by non-blinded statisticians using the SAS 9.4 randomization process and imported into IWRS. The IWRS will be accessed by investigators using their respective codes, and eligible subjects will be assigned a unique drug number in IWRS and will receive the study drug corresponding to the drug number. Subjects who have been randomized, regardless of whether they are receiving study medication or not, cannot be reassigned to other subjects if the study is terminated for any reason.

Cohort 1 will be performed in a double-blind manner. From the time of randomization, their treatment will be blinded, as well as the investigator, study team and anyone involved in the trial until the database is locked. The study drugs will also be blinded by non-blinded personnel not involved in this study, according to a drug randomization coding list provided by non-blinded statisticians. The computer program generating the randomization codes and the randomization code sheet will be used as a blinded base and kept securely by the unblinded team. The blinding will be kept strictly confidential until the final blinding, except in the circumstances such as emergency unblinding or suspected unexpected serious adverse reactions, in which case individual blinding may be performed by designated project personnel. Blinding personnel involved in the execution of the trial will not be informed of any of the subject’s blinding status until final blinding is completed, except in cases of emergency blinding.

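### Exclusion criterion 14 (less than 80% of study drink taken) cannot be assessed before randomisation, so as written it can act only on children already randomised, and its denominator is undefined

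*Protocol article*

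**What the plan says.** The exclusion list in section 2.2 opens with a bar on entry: "Subjects meeting any of the following exclusion criteria will not be allowed to participate". Its last item is "Poor compliance (i.e., therapeutic drinks taken at less than 80%), using the following formulas to estimate". Two formulas follow. The first takes the dose as the total less what remains; the second is "Adherence rate (a quantitative indicator of adherence) = (dose taken/total amount) x 100" per cent. Neither states a unit (drink, bacterial liquid or bottles) or a period (a phase or the whole course).

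On timing, section 2.1 describes consent and screening and continues: "They will then be randomly allocated to either the trial or control group in a 2:1 ratio". Section 2.4 says that "eligible subjects will be assigned a unique drug number in IWRS and will receive the study drug corresponding to the drug number". Section 2.5.2.1 puts bowel preparation at D-6 to D-1 and the first study drink at D1 to D7.

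On amounts, the same section gives for week 1 "approximately 700 mL of the therapeutic drink (containing 66 mL of bacterial liquid or placebo) orally over 3 to 5 consecutive days", and for the intensive phase "approximately 60 mL of the treatment drink (containing 6 mL of bacterial fluid or placebo) once a week for 3 weeks". Maintenance is 8 weekly doses of about 10 mL of drink, each with 0.6 mL of bacterial liquid or placebo.

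**The concern.** An exclusion criterion must be knowable before a child is randomised. The share of study drink taken is not. If the criterion is followed as written, the only children it can reach have already been allocated.

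The article itself gives reasons why intake may depend on treatment or prognosis. Section 2.5.1 adjusts intake to the volume the child can tolerate. Section 3 cites diarrhoea and nausea as the typical events with oral FMT capsules, and it stops further FMT after a serious adverse event. Selecting on intake is therefore selecting on something that treatment may influence, and the arms that remain need not be comparable.

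Three stated endpoints are exposed: the primary CARS change, the incidence of adverse events, and the acceptance scores. Children who refuse or cannot tolerate the drink carry much of the information on the last two.

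**Working it through.** **1. Can the criterion be assessed at entry?** The order is consent and screening (section 2.1), randomisation (2.1), drug number and issue of study drug (2.4), then first study drink on D1 (2.5.2.1). No drink is given before randomisation and no run-in is described. At entry the numerator of the adherence rate does not exist.

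**2. Inputs for the formula** (section 2.5.2.1). The article reports no adherence figure of its own to reproduce; 80% is only a threshold. I take the denominator as the whole planned course, by volume.

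| Phase | Drink, mL | Share | Bacterial liquid, mL | Share |
|---|---|---|---|---|
| Week 1 | 700 | 72.9% | 66 | 74.3% |
| Intensive | 3 × 60 = 180 | 18.75% | 3 × 6 = 18 | 20.3% |
| Maintenance | 8 × 10 = 80 | 8.3% | 8 × 0.6 = 4.8 | 5.4% |
| Total | 960 | 100% | 88.8 | 100% |

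**3. Adherence = amount taken / total, under different patterns**

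| Pattern | By drink | By liquid | Against 80% |
|---|---|---|---|
| All 3 intensive doses missed | 780/960 = 81.25% | 70.8/88.8 = 79.7% | passes / fails |
| 10 of 11 weekly doses missed (2 intensive, 8 maintenance) | 760/960 = 79.2% | 72/88.8 = 81.1% | fails / passes |
| 9 of 11 weekly doses missed (1 intensive, 8 maintenance) | 820/960 = 85.4% | 78/88.8 = 87.8% | passes both |
| All 8 maintenance doses missed | 880/960 = 91.7% | 84/88.8 = 94.6% | passes both |
| 70% of week 1, all 11 weekly doses | (490 + 260)/960 = 78.1% | (46.2 + 22.8)/88.8 = 77.7% | fails both |
| Stopped after a complete week 1 | 700/960 = 72.9% | 66/88.8 = 74.3% | fails both |

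The first two rows show the unit reversing the verdict. The last row shows that a child whose FMT is stopped after week 1, for instance for a serious adverse event under section 3, would meet the exclusion criterion on either measure.

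**4. Dependence on the reading.** If bottles were counted instead, an assumed 11 + 3 + 8 = 22 bottles would put week 1 at 11/22 = 50%, and at most 4 weekly doses could be missed (18/22 = 81.8%; 17/22 = 77.3%).

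**5. Power, as illustration only.** Section 2.3 gives 42 children at 2:1, one-sided alpha of 5 (read as 5%), 80% power, a 5-point reduction in the FMT group and 15% dropout. It gives no SD and no placebo change. Taking 42 × 0.85, about 36 evaluable (24:12), and assuming that the 5 points are the between-group difference, the implied SD is 5 / [(1.645 + 0.842) × √(1/12 + 1/24)] ≈ 5.7. If a further 5%, 10% or 20% were lost to the compliance rule on top of dropout (assumed rates), power would fall from 80% to about 78%, 76% or 72%. Nothing in the article shows whether poor compliers are already counted in the 15%.

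**The case against.** The strongest reply is that no randomised child is said to be removed from anything. Section 2.2 speaks of participation, and section 2.6 drops no one for poor compliance. Analysis sets are usually defined in a statistical analysis plan, which is not shown, and this article is a condensed account. That stands: a reader might infer that the plan discards poor compliers from the primary analysis and so breaks the randomised comparison, but the article does not say so. It does not remove the point, because an eligibility rule that can only be met after randomisation is wrong where it stands, and a later analysis plan does not correct the protocol's eligibility list.

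A second reply is that a volume ratio is a reasonable exposure measure. Section 5 explains that week 1 carries a high bacterial dose on purpose, and the bacterial content of the bottles in section 2.5.1 scales with their volume. That also stands. A reader might conclude from the 73–74% weight of week 1 that the formula is an error, but the documents support only that it registers late missed doses weakly and leaves its unit and period open. Likewise, the claim that a child could miss 10 of 11 weekly doses and still pass is true only by bacterial liquid. By drink, which is what criterion 14 names, that child fails, and the maximum is 9 of 11.

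Third, placebo matched on appearance, smell and weight reduces the chance that refusal differs by arm. It does so only in part, since side effects can still differ.

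**Conclusion.** The point holds in this form: criterion 14 cannot be assessed at entry and, taken literally with the opening sentence of the list, disqualifies randomised children on post-randomisation behaviour. This rests on the stated order of randomisation and first drink and on the absence of any described run-in. The bias is a risk, not a demonstrated fact, and its size and direction cannot be derived from the article.

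A reader might try to put a figure on it: with 20% of FMT children non-compliant and without benefit, and the rest gaining 5 points, the effect would be 0.8 × 5 = 4.0 in all randomised children against 5.0 after exclusion. The documents do not support that figure. The 20% and the zero benefit are assumed, a child just under the threshold has had most of the dose, and section 2.3 gives 5 points as the FMT-group reduction, not as the difference from placebo.

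The undefined denominator is a separate, smaller defect. On cumulative volume, drink and liquid give opposite verdicts in the two patterns shown, each close to 80%. The weight of week 1 is a property to report alongside the result, not a mistake.

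**What to change.** - Delete item 14 from the exclusion criteria in section 2.2.
- State that all randomised children stay in follow-up and in the primary comparison as randomised, whatever their adherence. This concerns follow-up and analysis only and changes no dosing or stopping rule.
- Use the 80% threshold only to define a supportive per-protocol set.
- For that set, fix the denominator: name the unit (drink, bacterial liquid or bottles) and the period.
- As a useful supplement, also report the share of the 11 weekly doses taken, since missing all 8 maintenance doses still scores 92–95% by cumulative volume.

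The cost is protocol wording and one analysis-set definition. The formula already needs the remaining dose; Table 1 shows no row for returned drink, so confirm that it is recorded per dose. The statistical downside is that non-compliers kept in the comparison may dilute the estimate slightly.
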